## Abstract

**Background:**

Due to the increasing use of online health information, symptom checkers have been developed to provide an individualized assessment of health complaints and provide potential diagnoses and an urgency estimation. It is assumed that they support patient empowerment and have a positive impact on patient-physician interaction and satisfaction with care. Particularly in the emergency department (ED), symptom checkers could be integrated to bridge waiting times in the ED, and patients as well as physicians could take advantage of potential positive effects. Our study therefore aims to assess the impact of symptom assessment application (SAA) usage compared to no SAA usage on the patient-physician interaction in self-referred walk-in patients in the ED population.

**Methods:**

In this multi-center, 1:1 randomized, controlled, parallel-group superiority trial, 440 self-referred adult walk-in patients with a non-urgent triage category will be recruited in three EDs in Berlin. Eligible participants in the intervention group will use a SAA directly after initial triage. The control group receives standard care without using a SAA. The primary endpoint is patients’ satisfaction with the patient-physician interaction assessed by the Patient Satisfaction Questionnaire.

**Discussion:**

The results of this trial could influence the implementation of SAA into acute care to improve the satisfaction with the patient-physician interaction.

**Trial registration:**

German Clinical Trials Registry DRKS00028598. Registered on 25.03.2022

## Administrative information

Note: the numbers in curly brackets in this protocol refer to SPIRIT checklist item numbers. The order of the items has been modified to group similar items (see http://www.equator-network.org/reporting-guidelines/spirit-2013-statement-defining-standard-protocol-items-for-clinical-trials/).

## Introduction

### Background and rationale {6a}

According to a representative survey among the German population, 20% of the participants named the internet as their primary source of health information [1]. Especially patients seeking emergency care services use online information to self-assess their symptoms and search for potential diagnoses prior to their visit [2–4]. In recent years, special applications have been developed for this purpose: symptom assessment applications (SAA) are smartphone- or web-based applications for laypersons providing an individualized assessment of the entered health complaints by providing suggestions on likely diagnoses and a categorization of their treatment urgency. In Germany, the number of users of these systems has risen to 13% in 2020 [5]. Such apps provide a convenient option for patients to obtain information in preparation for contact with the physician. SAA could empower patients to provide the physician with more specific information during anamnesis and support them to prepare their own questions [6]. This, in turn, could have a positive impact on patient-physician interaction. While studies on SAA accuracy of assessment already exist [7–11], current research is insufficient to evaluate the effects of SAA on their users, as well as their received care and the treating physicians. Thus, it is unclear whether the individual value of symptom checkers translates into a meaningful and quantifiable improvement of care delivery, patient satisfaction, and an improvement of the physician-patient relationship. Two observational studies showed positive effects of using Google as a source of online health information on the perceived quality of received care and patient-physician interaction [3, 4], but a randomized controlled trial could not confirm this effect [2]. To this end, it is possible that reported positive effects are not attributable to the information search per se, but rather to the fact that patients who obtain health information on their own are also better able to seek care. In contrast to internet search-based online health information seeking, symptom checkers guide their users through the self-assessment process and provide more custom-tailored information, for example, on plausible diagnoses and appropriate therapies. Thus, SAA recommendations might constitute a fruitful basis for the patient’s interaction with the treating physician. Particularly in the emergency department (ED), with longer waiting times, symptom checkers could be integrated to bridge waiting times in the ED and take advantage of potential positive effects. Our study therefore aims to assess the impact of SAA usage as a special type of online health information on the patient-physician interaction and care delivery in the ED.

### Objectives {7}

#### Primary objective

To investigate the impact on patients’ satisfaction with the patient-physician interaction of a SAA prior to the first physician encounter among self-referred walk-in patients in the ED setting.

#### Secondary objectives

To investigate the impact of a SAA prior to the first physician encounter among self-referred walk-in patients in the ED setting on satisfaction with the received care at the end of the ED visit.To investigate the impact of a SAA prior to the first physician encounter among self-referred walk-in patients in the ED setting on anxiety of participants.To investigate the impact of a SAA prior to the first physician encounter among self-referred walk-in patients in the ED setting on physicians’ satisfaction with the patient-physician interaction after the patient-physician encounter.

#### Other objectives

4.To examine the level of trust in the SAA after using it.5.To assess the usability and usefulness of the app-based self-assessment as rated by the participants.6.To translate and validate a German version of the mHealth App Usability Questionnaire (MAUQ).7.To assess participants’ decisional certainty in their stand-alone and app-supported triage recommendations.8.To assess diagnostic and triage accuracy of the app-based self-assessment.9.To assess the prognostic value of the triage to predict hospitalization and other clinical endpoints.10.To compare patients’ and physicians’ appraisals of patients’ eHealth-literacy, and the usability and usefulness of the SAA for patients.

### Trial design {8}

The study is a parallel-group, multi-center superiority trial with a randomization allocation ratio of 1:1 to either using a SAA before the physician encounter or physician encounter only (standard care) among non-urgent, self-referred walk-in patients in the ED.

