### Eligibility criteria {10}

#### Inclusion criteria

Patients eligible for the trial must comply with all of the following at randomization:Age ≥ 18Treatment urgency assessed with the Manchester triage system: categorized as yellow (urgent, 30 min.), green (standard, 90 min.), or blue (non-urgent, 120 min.)Self-referred walk-inAdequate German or English language skillsThe patient is able to provide informed consent.

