### Recruitment {15}

Study nurses will approach patients in the waiting room of each study site to ask for participation in the study. Student assistants will assist study nurses in detecting and recruiting patients from the waiting rooms. Data collection is set to a time period of 6 months and the targeted sample size of 440 patients visiting Charité’s EDs in Berlin-Mitte and Berlin-Wedding (CCM and CVK), as well as Jüdisches Krankenhaus Berlin’s emergency practice of the association of statutory health insurance physicians (KV-Bereitschaftspraxis). It is assumed that it is realistic to reach the targeted numbers of patients since the number of patients presenting in the ED within the timeframe of 6 months is significantly higher than the number of participants needed for this study. Around 40,000 patients with the respective MTS categories (3 to 5) visited the EDs in a 6-month period in recent years (unpublished data).

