## Assignment of interventions: allocation

### Sequence generation {16a}

The allocation sequence will be generated by the Institute of Medical Informatics, applying a permuted block design with random blocks stratified by study center using computer-generated random numbers. The block size will be concealed until the primary endpoint will be analyzed. Throughout the study, the randomization will be conducted by the Institute of Medical Informatics. The randomization list remains with the Institute of Medical Informatics for the whole duration of the study. Thus, randomization will be conducted without any influence of the principal investigator, study personnel, or physicians.

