## Statistical methods

### Statistical methods for primary and secondary outcomes {20a}

R 4.0.2 or higher (R Core Team, 2022) and SAS 9.4 (SAS Institute, USA) will be used to perform statistical analyses. Baseline characteristics will be presented as percentages (binary data), median and interquartile range (ordinal data), and mean and standard deviation (continuous data). The primary efficacy endpoint is the mean difference in the patients’ rating of patient-physician interaction (PSQ-5) between the intervention group and the control group after patients have been treated (final value) and will be analyzed with a linear mixed model accounting for recruiting site. Secondary and exploratory efficacy endpoints will be analyzed using (generalized and mixed) linear models. Reporting will include the estimator, 95% confidence intervals, and respective *p* values. No adjustments of *p* values due to multiplicity are planned.

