### Methods for additional analyses (e.g., subgroup analyses) {20b}

Pre-planned subgroup analysis will be performed regarding the primary outcome variable in the subgroups in both study groups defined by the following criteria:AgeSexSocio-economic statusPrior usage of SAAeHealth Literacy (eHEALS)Self-reported health (MEHM)Technical affinity (ATI-S)Study sites

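### The design statement and abstract call the population non-urgent, but the inclusion criteria also admit patients triaged as urgent and standard, so a result under that label could be credited to a narrower population than the one enrolled

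*Protocol article*

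**What the plan says.** All references are to the protocol article.

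- **Population label.** Trial design {8} describes the comparison as one "among non-urgent, self-referred walk-in patients in the ED". The Methods paragraph of the abstract says "440 self-referred adult walk-in patients with a non-urgent triage category will be recruited in three EDs in Berlin".
- **Eligibility.** Under Inclusion criteria, patients qualify if their treatment urgency by the Manchester system is "categorized as yellow (urgent, 30 min.), green (standard, 90 min.), or blue (non-urgent, 120 min".
- **Feasibility.** Recruitment {15} states "Around 40,000 patients with the respective MTS categories (3 to 5) visited the EDs in a 6-month period in recent years". It gives no split by category.
- **Objective.** The primary objective concerns app use "prior to the first physician encounter among self-referred walk-in patients in the ED setting", with no restriction on urgency. The secondary objectives name the same population.
- **Randomisation and analysis.** The sequence is generated by "applying a permuted block design with random blocks stratified by study center using computer-generated random numbers". The primary endpoint "will be analyzed with a linear mixed model accounting for recruiting site". Section {20b} says "Pre-planned subgroup analysis will be performed regarding the primary outcome variable in the subgroups in both study groups" and lists age, sex, socio-economic status, prior app use, eHealth literacy, self-reported health, technical affinity and study site. Triage category is not listed.
- **Data.** Section {18a} includes the assigned MTS level and the waiting time in the routine clinical data.

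**The concern.** By the protocol's own labels, one of the three admitted categories is non-urgent and one is expressly urgent. Both statements cannot describe the same sample, and neither a fuller protocol nor an analysis plan could make both true.

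Readers and evidence reviewers often take the population of a trial from the abstract and the design statement. Nothing in the plan limits the number of yellow patients: there is no quota, and stratification is by center only. A sample with few yellow patients and a sample with many would both carry the non-urgent label. The Discussion wants the results to inform decisions on introducing the app into acute care, where the urgency of the patients tested is relevant.

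A secondary point is that triage level is set before consent and recorded, yet it is named neither in the primary model nor among the eight subgroup factors. No listed analysis would describe the result by triage category.

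**Working it through.** **1. Passages side by side**

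| Place | Population described |
|---|---|
| Abstract, Methods | non-urgent triage category |
| Trial design {8} | non-urgent walk-in patients |
| Inclusion criteria | yellow (urgent), green (standard), blue (non-urgent) |
| Recruitment {15} | MTS 3 to 5 |
| Primary and secondary objectives | self-referred walk-in ED patients, urgency not mentioned |
| Discussion | acute care, urgency not mentioned |

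The inclusion criteria and the recruitment estimate agree with each other, so admitting yellow is deliberate. The word non-urgent in the first two rows is the outlier.

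**2. Does the planned sample size depend on the label?**

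Inputs from Sample size {14}: standardised difference 0.3, two-sided alpha 0.05, power 0.80, drop-out 20%.

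- The exact two-sample t-test needs 175.4 per arm, rounded up to 176, so 2 × 176 = 352.
- 352 / (1 − 0.20) = 440.

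Both stated figures reproduce, and neither uses triage category.

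**3. What would the trial say about patients outside yellow?**

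The yellow share is not in the document, so it is assumed here. Evaluable patients per arm outside yellow = 176 × (1 − share). Power is by the exact t-test at a standardised difference of 0.3.

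| Assumed yellow share | Per arm outside yellow | Power in that subset alone |
|---|---|---|
| 20% | 141 | 71% |
| 40% | 106 | 58% |
| 60% | 70 | 42% |

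The trial was not sized for this subset. The table shows only that a claim about patients outside yellow could rest on much less than the nominal 80%.

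**4. What would baseline covariates add?**

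If covariates explain a fraction R² of the outcome variance, the effective standardised difference is 0.3 / √(1 − R²). R² is assumed and refers to MTS category, age and baseline VAS-A together.

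| R² | Effective difference | Power at 176 per arm |
|---|---|---|
| 0 | 0.300 | 80.1% |
| 0.02 | 0.303 | 80.9% |
| 0.05 | 0.308 | 82.1% |
| 0.10 | 0.316 | 84.1% |

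**5. What could a treatment-by-MTS interaction show?**

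Take the most favourable split, half yellow and half green or blue, and an interaction as large as the whole assumed effect (0.3 SD).

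- Standard error of the main effect: √(2/176) = 0.107.
- Standard error of the interaction: √(2/88 + 2/88) = 0.213, twice as large.
- z = 0.3 / 0.213 = 1.41, which gives power of about 29%.

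Uneven splits give less.

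**The case against.** The strongest reply is that this is a loose adjective in two places. The eligibility criteria are the operative text and spell out all three categories. The recruitment estimate uses the same range, and the objectives and Discussion carry no urgency restriction. Anyone who reads the eligibility section knows who was enrolled. This stands, and it limits the consequence. A reader might infer that the conclusions will be attached to the wrong population. The documents show only that they could be, if reported under the label in the abstract and the design statement.

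A reader might also infer that leaving triage out of the primary model is a fault. It is not. Randomisation is stratified by center and the model accounts for site, so analysis and design match. Omitting a baseline variable that was not a stratification factor from a linear model does not bias the randomised comparison. Further covariates may be fixed in an analysis plan that is not shown. A ninth subgroup factor is likewise optional, and its test would be weak.

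Finally, one might argue that yellow patients, with a 30-minute target, have less room to use the app. The document gives no support for a large difference: estimated completion time is around 8 minutes, and patients treated without waiting are excluded. A difference in delivery by category remains possible but is conjecture.

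What the reply does not remove is the contradiction itself.

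**Conclusion.** The population is misdescribed in the abstract and the design statement. Only one of the three admitted triage categories bears the non-urgent label, and the recruitment estimate confirms that the wider range is meant. A result reported under that label could be attributed to a narrower population than the one enrolled.

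The size of the discrepancy cannot be stated, because the share of yellow patients is not given. A claim that the result would be dominated by yellow patients therefore has no support in the document. No stated figure is wrong, and enrolment, sample size and the validity of the comparison in the enrolled mix are untouched.

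The covariate suggestion is an improvement and does not correct an error. Its gain, from 80.1% to about 81–84%, rests on an assumed R² of 0.02–0.10.

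**What to change.** **Required.** Reconcile Trial design {8} and the abstract with the inclusion criteria, so that all of them describe the population by the same MTS categories. Which categories should be eligible is for the investigators to settle. Report enrolment by MTS category in each arm. The cost is wording and one descriptive table from data already collected.

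**Optional, as a gain in precision.** Name MTS category, age and baseline VAS-A as fixed covariates in the primary linear mixed model in {20a}, before the data are analysed. Use VAS-A values recorded before randomisation, since {18a} allows parts of the baseline survey to be timed flexibly. No extra patients or measurements are needed.

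**Optional, exploratory.** Add a treatment-by-MTS analysis to the list in {20b}, labelled exploratory, with its low power stated (about 29% for an interaction of 0.3 SD at an even split). Report it as an estimate with a confidence interval, and do not read a non-significant interaction as evidence of equal effects.

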## Methods: participants, interventions, and outcomes

### Study setting {9}

The study is a local, multi-center ED-based study with three study sites located in Berlin, Germany. Two of the study sites are EDs of a large tertiary care hospital (Charité – Universitätsmedizin Berlin, Campus Mitte/Campus Virchow-Klinikum). One site is an emergency practice of the association of statutory health insurance physicians attached to the ED of a local hospital (Jüdisches Krankenhaus Berlin).

### Eligibility criteria {10}

#### Inclusion criteria

Patients eligible for the trial must comply with all of the following at randomization:Age ≥ 18Treatment urgency assessed with the Manchester triage system: categorized as yellow (urgent, 30 min.), green (standard, 90 min.), or blue (non-urgent, 120 min.)Self-referred walk-inAdequate German or English language skillsThe patient is able to provide informed consent.

#### Exclusion criteria

Patient treated without waiting timeCause of complaint known according to patientPatient requiring isolationPatient who would not be able to use a tablet according to the assessment of the study personnel on site or according to their own judgmentPatient consulted a symptom checker app for the current complaints prior to seeking health care

### Who will take informed consent? {26a}

Participants eligible for inclusion will be invited by study personnel to give written and verbal informed consent directly after the initial triage. The participant will be handed a copy of the Human Research Ethics Committee/Institutional Review Board-approved informed consent form. The right of a participant to refuse participation without giving reasons will be respected. The participant is free to withdraw from the trial at any time without giving reasons and without prejudicing the participant’s further treatment.

All site investigators and delegates will be trained and competent to participate according to the ethically approved protocol, principles of Good Clinical Practice (GCP), and the Declaration of Helsinki.

### Additional consent provisions for collection and use of participant data and biological specimens {26b}

Participants will be asked if they wish to be contacted for a separate study. This study consists of approximately 15-20 semi-structured qualitative interviews with patients from the intervention group. In addition, we will perform two focus groups with health care professionals (treating physicians and nurses, 6-10 per group) who treated study participants in the acute care setting.

There will be no collection of biological specimens beyond standard care.

## Interventions

### Explanation for the choice of comparators {6b}

Patients in the control group proceed as usual and only complete questionnaires at the beginning of their waiting period and at the end of the ED visit. Otherwise, they wait without further intervention and receive standard care to ensure that the experimental intervention can be compared to the regular ED procedure. In extraordinary circumstances, patients can be contacted via telephone for up to 72 h to reduce loss-to-follow-up.

### Intervention description {11a}

Eligible patients randomized to the intervention group will use the SAA Ada (© 2021 Ada Health GmbH: www.ada.com). Patients will be asked to use Ada once to assess their symptoms on a study tablet—which will be provided by the study nurses—while waiting in the ED before their first consultation with a physician. Once completed, they receive a list of possible diagnoses and an estimation of their complaints’ urgency from the SAA. The assessment and recommendations are printed by the study personnel and will be provided to the treating physician before the ED consultation. Thus, the intervention is the same for all patients, but the received advice is tailored to their prior responses when using the symptom checker.

### Criteria for discontinuing or modifying allocated interventions {11b}

Patients will use the SAA with an estimated mean completion time of around 8 min. If patients decide to not finish the assessment, e.g. withdrawal of consent, they will stop using the app and are considered according to the randomized group in the intention to treat analysis but excluded from per protocol analysis.

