### Relevant concomitant care permitted or prohibited during the trial {11d}

No interventions are prohibited. However, the use of other SAA or online health information while waiting is discouraged.

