### Methods in analysis to handle protocol non-adherence and any statistical methods to handle missing data {20c}

The primary population for analysis of efficacy will be the intention-to-treat population (ITT). In addition, a per-protocol analysis (PP) and a full analysis set (FAS) will be performed.

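### The one stated per-protocol exclusion can arise only in the intervention arm, so the supplementary per-protocol comparison is open to selection bias; a complier average causal effect would answer the same question better

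*Protocol article*

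**What the plan says.** The rule is in the protocol article, section {11b}: "If patients decide to not finish the assessment, e.g. withdrawal of consent, they will stop using the app". Such patients are then "considered according to the randomized group in the intention to treat analysis but excluded from per protocol analysis".

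Other sections bear on it:

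- Section {6b}, on the control group: "Otherwise, they wait without further intervention and receive standard care". Controls are not given the app.
- Section {11d} prohibits nothing, but says that "the use of other SAA or online health information while waiting is discouraged". It does not link such use to membership of any analysis set.
- Section {20c} makes intention to treat the primary efficacy population and adds: "In addition, a per-protocol analysis (PP) and a full analysis set (FAS) will be performed". It does not define membership of the per-protocol set.
- Section {20a} analyses the primary endpoint with a linear mixed model that accounts for recruiting site. It names no other covariate.
- Section {8} describes a "parallel-group, multi-center superiority trial with a randomization allocation ratio of 1:1".

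**The concern.** Finishing the app is behaviour after randomisation, and it is observed in one arm only. Applying the stated rule leaves finishers in the intervention arm. The control arm keeps everyone, including patients who would not have finished had they been given the app. If the two kinds of patient would rate the physician encounter differently anyway, the per-protocol contrast mixes that difference with the effect of the app. Adjustment for site does not remove it. The outcome is self-rated satisfaction in an open-label trial, so such a difference is plausible.

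At stake is how the supplementary result is read. A per-protocol estimate is easily taken as the effect in patients who actually used the app, and under this rule it need not be that.

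A second, smaller problem lies in the same sentence. It gives withdrawal of consent as an example of not finishing the app. These are different events. A patient who merely stops the app can still complete the PSQ after the encounter; one who withdraws consent generally cannot. Running them together invites a site to omit the final survey for app-stoppers, which would lose primary outcome data in the intervention arm only.

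**Working it through.** **The plan's own figures.** Section {14} uses a 5-point difference and a standardised difference of about 0.3, which implies an SD of 5/0.3 = 16.67. A two-sample t-test at two-sided 0.05 with power 0.80 needs 175.4, so 176 per arm (power 0.801). Total 352, and 352/0.8 = 440. The stated sample size reproduces and is not in dispute. The 5 points, the SD and the 176 per arm serve below only as a scale.

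**Bias formula.** Let p be the share of patients who would not finish the app if offered it, and g the gap in mean PSQ, without the app, between finishers and non-finishers. By randomisation p is the same in both arms.

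- Control mean = (finisher mean) − p × g.
- Per-protocol intervention mean = (finisher mean) + (effect in finishers).
- Per-protocol difference = (effect in finishers) + p × g.

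The documents give neither p nor g, so both are assumed over a range. The rejection rate is for a true effect of zero, with 176 controls, 176 × (1 − p) intervention patients and SD 16.67.

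| p | g (points) | Bias p × g | Share of 5 points | Two-sided rejection rate |
|---|---|---|---|---|
| 5% | 2 | 0.10 | 2% | 0.050 |
| 5% | 5 | 0.25 | 5% | 0.052 |
| 5% | 10 | 0.50 | 10% | 0.059 |
| 10% | 2 | 0.20 | 4% | 0.051 |
| 10% | 5 | 0.50 | 10% | 0.059 |
| 10% | 10 | 1.00 | 20% | 0.085 |
| 20% | 2 | 0.40 | 8% | 0.055 |
| 20% | 5 | 1.00 | 20% | 0.083 |
| 20% | 10 | 2.00 | 40% | 0.186 |

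If g = 0 there is no bias. If non-finishers would be the more satisfied group, g is negative and the bias runs against the app.

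**What the alternative does.** Take p = 10%, g = 5, a true effect of 5 points in finishers and none in non-finishers.

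- Intention to treat: 0.9 × 5 = 4.5.
- Per protocol: 5 + 0.1 × 5 = 5.5.
- Complier average causal effect: 4.5/0.9 = 5.0, whatever the value of g.

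**What it costs in precision** (p = 10%, true effect zero, 176 per arm).

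- Per-protocol standard error: 16.67 × √(1/176 + 1/158.4) = 1.83, a 95% half-width of 3.58.
- Intention-to-treat standard error: 16.67 × √(2/176) = 1.78.
- Complier standard error: 1.78/0.9 = 1.97, a half-width of 3.87, about 8% wider than per protocol.

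**If the exclusion restriction fails.** If partial use changed satisfaction in non-finishers by e points, the complier estimate would be off by p × e/(1 − p). With p = 10% and e = 1 (assumed), that is 0.1 × 1/0.9 = 0.11 points.

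**The case against.** The strongest reply is that this is a general limitation of per-protocol sets, in a supplementary analysis of a superiority trial. Intention to treat is primary, non-finishers stay in their randomised group there, and no stated decision rule depends on the per-protocol result. That stands.

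A reader might infer that the per-protocol set removes intervention patients only. The article does not establish this. Section {11b} deals with discontinuing the intervention and never says that its criterion is the sole one. Section {20c} leaves membership undefined, and the full definition may sit in a document not shown. What can be said is that the only exclusion stated is one-sided. Since section {11d} prohibits nothing, a control who consults a symptom checker while waiting breaks no rule in the article.

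A reader might also infer that the per-protocol estimate is biased, and in the app's favour. Neither follows. Size and sign depend on two unknown quantities. Patients unable to use a tablet are already excluded at entry ({10}), the task takes about 8 minutes ({11b}), and vouchers reward completing the study ({11c}), so p may well be small. The 20% in section {14} is drop-out attributed to ED patient flow, not abandonment of the app. Controls who use a symptom checker would, if such tools help, shrink the contrast.

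Against the remedy it can be said that, with non-completion on one side only, the complier estimate is essentially the intention-to-treat estimate divided by the completion rate, and that its exclusion restriction is open to doubt: the trial is open-label and non-finishers have partly used the app. Both are fair. But the rescaled estimate keeps the randomised comparison, which the per-protocol one does not. The restriction is also reasonably plausible, because the list of diagnoses and the printout for the physician come only after completion ({11a}).

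On consent, the article says only that these patients stop using the app, not that they miss the later survey. The point is therefore one of clarification.

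**Conclusion.** The concern holds in limited form. The stated exclusion depends on post-randomisation behaviour that only the intervention arm can show, and the site-adjusted model would not remove the resulting selection. The supplementary per-protocol comparison is open to a bias of about p × g: 0.5 points at 10% and 5 points, and 0.1 to 2.0 points over the range examined. All of these rest on assumed inputs, and the sign is not certain. The documents do not support reading this as a threat to the trial's main result, since the rule leaves the primary intention-to-treat comparison intact. It is a modest, cheap improvement to a secondary analysis, together with one sentence that needs clarifying.

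**What to change.** 1. Estimate the effect of completing the app as a complier average causal effect: two-stage least squares with randomised arm as instrument, completion of the study assessment as exposure and site as covariate, in all randomised patients with a PSQ. With the exposure defined as the study assessment, controls are unexposed by design, and any app they use on their own is part of the control condition. Completion can be taken from the in-app reports already saved under section {18a}.
2. Label any per-protocol result as supportive only.
3. In section {11b}, separate stopping the app from withdrawal of consent, and say that patients who only stop the app remain in the study and still receive the survey after the physician encounter (t4 in Table 1).
4. Optional: a t4 question in both arms on use of any symptom checker while waiting. Recruitment began in April 2022, so the item would be missing for patients already enrolled, and an amendment needs ethics approval ({25}).

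Item 1 costs a few lines of code, a wider confidence interval (about 8% wider than per protocol in the example) and an exclusion restriction that must be stated and discussed, given the open-label design and partial use by non-finishers. Item 2 costs nothing. Item 3 costs one sentence, with whatever approval a protocol change requires.
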